#### Sample size and power

Based on preliminary MEDIC registry data, we anticipate approximately 580 acute PE patients per site over the trial period, providing ample power for all outcomes. With a complete cluster-randomized stepped-wedge design, we'll have over 99% power to detect our hypothesized increase in the proportion of acute PE patients managed without hospitalization from 12 to 25%. Sensitivity analyses will ensure robustness across different scenarios.

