### Site eligibility and recruitment

The study will be conducted across 12 centers participating in the MEDIC program [16, 17]. MEDIC comprises over 50 hospital emergency departments, collectively processing more than 2 million visits annually, involving over 1200 emergency physicians. The MEDIC registry records data from over 2500 patients with acute pulmonary embolism (PE) each year. These sites encompass a mix of urban and non-urban, as well as academic and community settings, with more than half serving patient populations with over 20% non-white demographics, facilitating the study of implementation disparities.

A subset of MEDIC sites were identified as eligible for participation in this trial. Specifically, sites were considered eligible to participate if:They had an active MEDIC clinical champion who could facilitate implementation activities;They had an acute PE volume of ≥ 80 diagnoses in the 2022 calendar year.

All eligible sites were contacted by one of the study leaders ([name]), an ED clinician, to confirm eligibility and interest in study participation. Most sites were contacted through their existing MEDIC clinical champion by phone or email between January and May 2023. Of the 15 total sites that were contacted, 12 agreed to participate.

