### MEDIC registry data

Data collection for the majority of our implementation and clinical effectiveness outcomes will be obtained for analysis through the existing central MEDIC Data Registry. All MEDIC sites, including the 12 study sites, currently contribute electronically extracted data into this registry. This includes data from all ED visits with imaging ordered to evaluate for possible acute PE (primarily computed tomography [CT]). For our purposes, results of the CT scan along with ICD-10 diagnosis codes (I26) will be used to identify a cohort of patients with acute PE. Additional data collected for each case include key demographics, comorbidities, medications and other treatments administered, and disposition data (i.e., hospital admission, home discharge). These data undergo regular audits by the MEDIC team (distinct from our study team) to ensure data accuracy and completeness. Data on key outcomes will be available from the pre-implementation phase through the end of the maintenance phase (a minimum of three months after the 12-month post-implementation phase).

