### Primary outcome

To assess changes in the proportion of patients with acute PE discharged from the ED rather than admitted to the hospital, we will employ mixed-effects logistic regression to analyze the data. The dependent variable will be a patient-level measure of hospital discharge (binary yes/no). The primary independent variables will be a measure of pre-post implementation state, a time variable, and a categorical variable of the group assignment. We will include an interaction between the categorical group assignment variable and the pre-post implementation state variable. Fixed effects covariates will include key patient characteristics (e.g., age, sex, race/ethnicity, insurance status, comorbidity score) and random effects for the site. Individual sites will be included as a random effects variable in the model. In the primary analysis, we will exclude the 6-month implementation period in order to best compare pre- vs. post-implementations states. In an exploratory analysis, we will include a 3-phase analysis of the pre-implementation, active implementation, and post-implementation phases.

In a secondary analysis, we will also include data from non-participating control sites. These sites will be assigned to the pre-intervention state during the entire time period. Any site that does not care for adult patients (e.g., pediatric hospital) or patients with acute PE (e.g., psychiatric hospital) will be excluded from this analysis.

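### On the protocol's apparent timeline, 580 acute PE patients per site would use about 93–101% of the annual volume stated for the whole registry of over 50 EDs, and nothing printed resolves the conflict

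*Protocol article*

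**What the plan says.** All places are in the protocol article.

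- *Sample size and power*: "we anticipate approximately 580 acute PE patients per site over the trial period, providing ample power for all outcomes". The basis is preliminary registry data that are not shown. The same paragraph states power above 99% for a rise from 12% to 25% in a complete stepped wedge.
- *Site eligibility and recruitment*: "The study will be conducted across 12 centers participating in the MEDIC program"; "MEDIC comprises over 50 hospital emergency departments"; "The MEDIC registry records data from over 2500 patients with acute pulmonary embolism (PE) each year". Eligible sites needed at least 80 acute PE diagnoses in 2022. "Of the 15 total sites that were contacted, 12 agreed to participate".
- *MEDIC registry data*: "All MEDIC sites, including the 12 study sites, currently contribute electronically extracted data into this registry". Outcome data run from the pre-implementation phase to the end of maintenance.
- *Implementation mapping* and *Evaluation of implementation and effectiveness outcomes*: 3 months pre-implementation, 6 months implementation, 12 months post-implementation, then maintenance of 12 months for Group 1 and 3 months for Group 4.
- *Primary outcome*: "we will exclude the 6-month implementation period" from the primary analysis.

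**The concern.** The cluster size of 580 is the only sample-size input printed, and both power statements rest on it. A reader can test it against the registry's annual volume, and on the timeline given it would leave almost no acute PE cases for the other 38 or more EDs that feed the same registry. If the figure covers a longer calendar window than the trial, or more sites than the 12, then the number per site in the trial is smaller than stated.

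A second mismatch is that the count is described as covering the trial period, whereas the primary analysis uses that period less six months per site. The stated power is for a design with no such gap.

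**Working it through.** **Window.** Group 1: 3 + 6 + 12 + 12 = 33 months = 2.75 years. Group 4 has 3 + 6 + 12 + 3 = 24 months of its own phases, so it starts 9 months later and ends at the same time. The abstract speaks of start dates staggered over 12 months. Taking the full 12 gives 36 months at most. Counting every site for the whole window is the generous choice: starting each site's count at its own pre-implementation phase would shorten the window for later groups and raise the annual rate required.

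**Annual load implied by 580.** Total = 12 × 580 = 6,960.

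| Reading of the 580 | Years | Needed per year, 12 sites | Per site per year | Share of 2,500 |
|---|---|---|---|---|
| Whole window, 33 months | 2.75 | 6,960 / 2.75 = 2,531 | 211 | 101% |
| Whole window, 36 months | 3.00 | 6,960 / 3 = 2,320 | 193 | 93% |
| Analysed months only, 33 − 6 = 27 | 2.25 | 6,960 / 2.25 = 3,093 | 258 | 124% |

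On the 36-month reading, (2,500 − 2,320) / 38 = 4.7 cases a year remain for each other ED. For 580 to hold over 33 months with the other 38 EDs averaging 10 to 20 cases a year, the registry would need 2,531 + 380 = 2,911 to 2,531 + 760 = 3,291 a year.

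**What the printed figures would allow per site.** These are illustrations: they take 2,500 a year and 50 EDs at face value, and the averages for the other EDs are assumptions. Per-site rate = (2,500 − 38 × average) / 12. The 27-month column counts maintenance months as post-implementation.

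| Assumption | Per site per year | 33 months | 27 months |
|---|---|---|---|
| Eligibility floor | 80 | 220 | 180 |
| Other EDs average 30 | 113 | 312 | 255 |
| Other EDs average 20 | 145 | 399 | 326 |
| Other EDs average 10 | 177 | 486 | 398 |
| Other EDs have none | 208 | 573 | 469 |

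If 580 over 33 months were right, the analysed number would be 580 × 27 / 33 = 475.

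**Power.** The article gives no alpha, ICC or cluster autocorrelation. Assumed here: two-sided alpha 0.05, ICC 0.01 to 0.10, autocorrelation 1.0 or 0.8. Method: generalised least squares on site-by-period proportions, 4 sequences of 3 sites treated as independent, one common effect, residual variance 0.185 × 0.815, power = Φ(0.13 / SE − 1.96). The complete design has 5 periods. The version without the implementation period has 11 calendar quarters, with two dropped per site.

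| Design and time model | 580 per site | 312 per site | 220 per site |
|---|---|---|---|
| Complete, 5 periods | 98.5% to >99.9% | 96.1% to >99.9% | 93.2–99.9% |
| Implementation excluded, linear time | 97.1% to >99.9% | 90.6–98.9% | 83.3–95.0% |
| Implementation excluded, quarters as categories | 47.6–80.6% | 36.3–55.1% | 30.1–42.2% |

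Given 580 and a complete design, the stated power above 99% is reproduced in nearly every scenario. The exception is ICC 0.10 with autocorrelation 0.8, at 98.5%.

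**The case against.** The best defence is that nothing printed is strictly impossible. The registry volume is a lower bound. The trial period is never defined, and *Analyses* includes patients from before study participation, so a longer retrospective baseline may be meant. The 12 sites were chosen for volume, so a large share of registry cases is expected. All of this stands, and it is why the point is a conflict and not an impossibility. It does not remove the conflict: *MEDIC registry data* starts outcome data at the pre-implementation phase, no longer window or higher volume is stated, and a large share is not a share near 100%.

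It is also fair that counting implementation months is no error in itself, since they are used in the exploratory three-phase analysis. What remains is that the power statement does not say how many patients the primary analysis keeps.

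Three stronger readings are tempting and are not supported:

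- A reader might infer that 580 came from dividing the whole registry among 12 sites, because 2,500 × 2.75 / 12 = 573. The match depends on the window chosen (3 years gives 625), and the text does not describe such a step.
- A reader might infer that the trial is underpowered. The complete design at 220 per site still gives about 93–99.9%. The low values come mainly from dropping the implementation period while fitting quarters as categories, which gives only 48–81% even at 580. The plan says only that there will be a time variable.
- A reader might apply the 25–40% in *Background* to size the reach outcome. That range is the share who can be managed safely at home. Reach is defined by PESI class I–II, whose prevalence is not given.

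**Conclusion.** The point holds as a conflict between printed figures. On the apparent timeline of 33 to 36 months, 580 per site requires 2,531 to 2,320 acute PE patients a year from 12 sites, about 101% to 93% of the floor stated for the entire registry. If 580 means analysed patients only, the share is 124%.

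The true number per site cannot be derived from the article. It is 220 over 33 months at the eligibility floor, and about 310 to 490 if the other EDs average 30 to 10 cases a year. These rest on 2,500 and 50 being close to the real values, although both are lower bounds.

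Primary power may stay high with linear time: 83–95% at the lowest illustration with the implementation period excluded, under assumed ICC and autocorrelation. The defect is therefore an unsupported planning figure and a power statement for a design other than the one analysed. It is not a demonstrated loss of power. The claim of ample power for every outcome has no figure behind it for the PESI I–II reach outcome.

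**What to change.** 1. Confirm or replace 580 with the sum of the 12 sites' own registry counts, and state the calendar window it covers. If a retrospective baseline is included, say so and align *MEDIC registry data* with it.
2. Give the number left per site after the implementation period is excluded.
3. Restate primary power for that number under the planned form of the time variable, with ICC and autocorrelation shown as assumptions over a range.
4. Delete the statement of ample power for all outcomes, or support it with a separate calculation for reach using an observed PESI I–II share.

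Cost: one registry query (2022 volumes were already used to judge eligibility), a rerun of the power calculation and a few changed sentences. No extra patients or sites are needed. The restated number and power may be less favourable.

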## Discussion

This pragmatic, stepped-wedge implementation trial aims to implement and evaluate a four-component intervention to increase the use of evidence-based outpatient management for patients presenting to the ED with a low-risk acute PE. If shown to be effective, this trial will provide a model for implementing similar strategies at hospital ED’s across the US as well as provide a framework for other implementation efforts in the ED setting.

This study represents a critical advancement in the field of implementation science for acute PE management by incorporating several innovative elements. First, unlike previous efforts focusing primarily on effectiveness outcome measures, this study deeply integrates theory-informed implementation and de-implementation frameworks. To guide the implementation process, this study pioneers the use of Implementation Mapping [11] in the ED setting, offering a structured approach to intervention development and tailoring. By applying this approach across diverse sites, this study aims to establish a model for multi-site collaborative-based quality improvement and implementation efforts broadly across a wide range of clinical diagnoses and management domains.

Second, this study directly addresses the heuristics commonly used by ED clinicians in disposition decision-making. Through innovative strategies derived from behavioral economics, such as pre-commitment and point-of-care nudges, this study aims to facilitate behavior change and improve the appropriateness of clinical decision-making.

Two unique features of this study deserve further discussion. First, is the conduct of this implementation trial within an existing quality improvement collaborative. These networks often represent diverse health systems and have existing data collection infrastructure that reduces the burden of data management for the research team. In this case, the MEDIC collaborative has an ongoing effort to optimize CT use for patients suspected of having PE. As such, there is a culture of healthcare quality improvement around the diagnosis of acute PE that facilitates interest and participation in this project. However, no ongoing project within each of these centers addresses hospitalization versus outpatient acute PE management, minimizing potential contamination. Given that all MEDIC sites are already collecting and contributing data to the MEDIC data registry, no additional patient-level data is required for participation in this stepped-wedge implementation trial. Conducting implementation trials within an independently funded collaborative reduces costs for all involved parties: the primary research team reduces infrastructure costs while the collaborative benefits from rigorous implementation science research provided by external funding (in this case, the National Heart, Lung, and Blood Institute) that lowers the barriers to practice change. This is a promising model for low-cost/high-value implementation trials in the future.

The second unique feature of this study is the innovative approach to measuring implementation fidelity. While the FRAME and FRAME-IS tools [18, 19] are well described in the implementation literature, few studies have adopted a categorical assessment of implementation. The quantitative assessment of implementation fidelity provided by these tools can be integrated into a multivariable regression model to help identify which adaptations may have a greater or lesser influence on key outcome measures.

Our study has important limitations. First, while our study includes 12 diverse hospital EDs across the state of Michigan, these sites may not represent the entire diversity of all hospital EDs in the US. Furthermore, practice variation from state-to-state and between the US and other countries may limit the generalizability of these findings. Second, data collection will rely on the existing MEDIC collaborative data registry. While this data is audited for accuracy and completeness, it does not have robust post-ED data included. Our safety analysis will focus on 30-day events using a data matching protocol with Medicare, Medicaid, and private insurer claims data when available. However, not all patients will have complete post-ED claims for these analyses.

In conclusion, innovative implementation strategies are needed to change ED clinician behavior and increase the use of evidence-based, guideline-recommended outpatient management of low-risk acute PE. This stepped-wedge trial will evaluate a four component intervention across 12 diverse hospital EDs participating in the MEDIC quality collaborative. If found to be effective and broadly adopted, this multi-component implementation program will provide a framework for nation-wide adoption of this high-value, evidence-based practice in the United States.

## Data Availability

The quantitative datasets are managed by the MEDIC quality collaborative and are not available for public access due to data use agreements within the network. Qualitative datasets will be made available upon reasonable request.

## Abbreviations

CQI: Collaborative Quality initiative
CT: Computed Tomography
DOAC: Direct Oral Anticoagulant
ED: Emergency Department
HER: Electronic Health Record
FRAME: Framework for Reporting Adaptations and Modifications – Expanded
FRAME-IS: Framework for Reporting Adaptations and Modifications to Evidence-based Implementation Strategies
ICD-10: International Classification of Diseases, Tenth Revision
MEDIC: Michigan Emergency Department Improvement Collaborative
ORCA: Organizational Readiness to Change Assessment
PE: Pulmonary Embolism
PESI: Pulmonary Embolism Severity Index
RE-AIM: Reach, Effectiveness, Adoption, Implementation, Maintenance (framework for evaluation)
sPESI: Simplified Pulmonary Embolism Severity Index
